### Study design

The present project, which was also registered at www.drks.de before the start of data collection, contains two subsequent steps: (1) a PTSD screening in a large and representative sample of juvenile refugees from the DRC that will serve to identify participants eligible for inclusion in the intervention. A cross-sectional analysis comparing the physical activity levels of the refugees according to their PTSD symptom severity will serve to identify and balance potentially confounding variables. With regard to cross-sectional studies, it is difficult to make causal inferences because it is unknown if the parameter itself (e.g., being cardiovascularly fit) caused the benefit (e.g., reduced symptoms) or if other factors might have accounted for the resultant differences [49]. Therefore, (2) a longitudinal, prospective, and RCT will be implemented covering the ET intervention and two control conditions. *Group* (Exercise Training = ET, Alternative Intervention = AI, and Waiting-list Control = WC) serves as the between-subject factor. Eligible participants will be randomly assigned to one of the three conditions. The participants’ age, their traumatic load indicated by the number of experienced traumatic event types, the baseline PTSD symptom severity, and their physical activity level will serve as matching criteria across groups. The study utilizes a double-blind RCT design.

The *ET group* is subjected to an ET of 60–80% of the maximal heart rate (HR_max_). The *AI group* serves as the placebo group and receives fine and gross motor body coordination exercises through playful balance, bilateral coordination, hand-eye coordination, and leg-arm coordination exercises [49]. With such a sham-controlled study, it will be examined whether the expected changes in cortisol levels and symptom severity in PTSD patients are attributed to chronic exercise and no other influencing factors [50]. The *WC group* serves as a no-treatment control and is measured at the same intervals as the treatment group. It will not be implemented until the ET and AI groups have finished their second follow-up (t_4_). Introducing a second control group with the alternative intervention is mandatory to differentiate beneficial effects of miscellaneous physical activity from standardized ET. This is not only important to investigate a potential cross-cultural effectiveness of ET but also serves to justify the specific training requirements of ET and the need for sufficient resources in order to build up sustainable intervention programs. The flow diagram is presented in Fig. 1.

**Fig. 1 Fig1:**
[figure not shown]
Participant flow diagram

To assess the impact of chronic exercise on PTSD symptoms and cortisol profiles, repeated measurements with *time* (baseline (t_1_), interim test (t_1b_), post test (t_2_), 3-month follow-up (t_3_), and 6-month follow-up (t_4_)) as the within-subject factor will be conducted on the primary outcome measures *PTSD symptom severity* and awakening *cortisol profiles*. At eligibility (t_0_), the diagnosis will be verified and co-morbid diseases will be identified. In addition, at baseline (t_1_), the PTSD symptom severity, relevant information about the participants’ trauma and flight history, as well as their exposure to early life adversities will be assessed. As physiological measures, cortisol and DHEA levels will be determined. The assignment of participants to one of the three groups will be conducted afterwards. An interim measuring time point (t_1b_) at 4 weeks after the respective intervention will serve to adjust the training to the individual participant’s progress in the two exercise groups in order to assure that the ET stays over 60% HR_max_ after the 8-week interventional phase at the post test (t_2_). The baseline measures will be repeatedly assessed at the post test as well as the two follow-up measuring points (t_3_ and t_4_; see Fig. 2 and Additional file 1).

**Fig. 2 Fig2:**
[figure not shown]
Measures and assessment points used in the study

### Interventions

#### Exercise Training (ET) group

The participants in the ET group will attend three exercise sessions every week for a total number of 8 weeks. That makes this training a chronic exercise intervention [11]. Every unit takes 45 min. Two local and experienced trainers from Uganda instruct identical classes of 25–35 participants. Each session will be performed with high intensity with a HR_max_ of 70–85%. In our preliminary work, significant cortisol and testosterone increases were found by implementing an acute exercise of 70–85% HR_max_, but not with 50–65% HR_max_ [24]. The training program will focus on improvement of cardiovascular fitness through running and running-based games of moderate to vigorous intensity (recorded on three occasions by F1 Polar HR monitors; Polar, Kempele, Finland) [49].

#### Alternative Intervention (AI) group

The aim of this group is to control the placebo effect by implementing a training program in which lower changes in cortisol and DHEA levels, and thereby a lower improvement in PTSD symptoms compared to the ET group, are expected. The participants will attend three 45-min sessions a week for a total number of 8 weeks. The training of the AI group will consist of very little strain, light stretching, and simple exercises that target posture and balance [51] as well as fine and gross motor body coordination through playful balance, bilateral coordination, hand-eye coordination, and leg-arm coordination exercises [49]. These sessions will also be conducted in a group setting by local and experienced trainers.

#### Waiting-list Control (WC) group

No specific intervention will be implemented. However, the ET intervention will be done with this group after the end of the measurement (t_4_).

### Measures

#### Screening

The *UCLA Child/Adolescent PTSD Reaction Index for DSM-5* (UCLA; [52]) is a screening tool recommended by the National Centre for PTSD to collect data about the kind of traumatic happening the participants experienced. It is a 24-item questionnaire assessed to DSM-V criteria for PTSD.

The *Mini International Neuropsychiatric Interview - Kid 7.0.2* (M.I.N.I.; [53]) represents a shortened psychiatric interview on the basis of DSM-V in order to help clinicians diagnose and evaluate the major psychiatric disorders. The test takes about 15–20 min and is performed in form of a standardized interview. The M.I.N.I. will help to identify acute co-morbid diseases relevant for eligibility of the participants.

#### Primary outcome

For the more in-depth baseline PTSD assessment, the *Clinical Administered PTSD Scale for DSM-5 Child/Adolescent Version* (CAPS-CA-5; [54]) will be applied. The CAPS-CA-5 is a 30-item structured interview for the assessment of PTSD based on DSM-5 criteria. The interview will take about 45–60 min and is considered the gold standard for assessing PTSD severity. The CAPS-CA-5 has excellent psychometric properties and has already been successfully administered in other East-African samples [55]. It will serve as the main psychological outcome variable.

#### Secondary outcomes

The Adapted version of the *Patient Health Questionnaire* (PHQ-A; [56]) for the use in adolescent samples will be used as a measure to assess the participants’ depressive symptomatology. It is a brief, nine-item measure that assesses clinically significant symptoms of depressive disorders and episodes in children ages 11–17 years.

The *Strengths and Difficulties Questionnaire* (*SDQ*; [57]) is a brief behavioral screening questionnaire that can serve to identify psychosocial, emotional, and behavioral problems. It is a widely used 25-item measure that has shown its usefulness in various studies and different populations with mental health problems.

The *Psychlops* [58] is a client-generated outcome measure for the assessment of the main psychological problem from the patients’ perspective. It is designed to measure longitudinal changes over the course of an intervention and provides different questions for the baseline, the interim, and the follow-up assessments. In this study, it will also help to capture the most significant mental health problems beyond the diagnosis-specific approach.

#### Hormonal analysis

The determination of the cortisol awakening response (CAR) will take place in following six samples:Sample 1 “awakening” in the morning as soon as the participants wake upSample 2 “post-awakening I” 30 min after taking the awakening sampleSample 3 “post-awakening II” 45 min after taking the awakening sample.Sample 4 “post-awakening III” 60 min after taking the awakening sampleSample 5 “post-awakening IV” at 9 a.m., collected in the schoolSample 6 “post-awakening V” at 11 a.m., collected in the school

Additionally, DHEA levels will be obtained at sample 1, sample 2, and sample 3 only. The samples will be independently collected in salivates by the participants. Saliva will be collected by either passive drooling into the tube or by chewing (for 2 min) the cotton provided with each tube. Participants must wait at least 10 min after smoking, consuming any food or drink, or teeth-brushing before collecting the saliva sample. Previous research has found different stimulation of salivary samples in children with chronic malnutrition [59]. Therefore, our implemented WC group provides the advantage of having a comparable outcome among traumatized children without any treatment condition. In addition, to control the possible influence of malnutrition onto hormonal samples, the Body Mass Index (BMI) and the skinfold thickness will be determined. Tubes will be labeled with patient identifier and returned to the laboratory via collection by the researcher. Upon arrival at the laboratory, tubes with saliva will be centrifuged to remove the upper salivary layer for subsequent measurement of cortisol and DHEA. The DHEA-to-cortisol ratio will be determined by dividing DHEA levels by the respective cortisol levels. The subjects will be informed that the sample has to be collected ± 5 min according to the respective agreed time point. Free cortisol levels in saliva will be measured using a commercially available chemiluminescence assay (IBL, Hamburg, Germany). The evaluation is carried out by [name] in Dresden, Germany.

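### Two saliva collection methods are permitted and neither is fixed within a participant, which can add avoidable variance to within-person hormone change

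*Protocol article*

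**What the plan says.** The Hormonal analysis section describes six timed cortisol samples per sampling day. On method it says: "Saliva will be collected by either passive drooling into the tube or by chewing (for 2 min) the cotton provided with each tube". Cotton comes with every tube, so both methods are available at every sample. On who does the sampling it says: "The samples will be independently collected in salivates by the participants". The participants are aged 13–16.

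The same tubes serve three hormone measures. On DHEA: "DHEA levels will be obtained at sample 1, sample 2, and sample 3 only". On the ratio: "The DHEA-to-cortisol ratio will be determined by dividing DHEA levels by the respective cortisol levels".

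In Study design (text after Fig. 1), time serves "as the within-subject factor will be conducted on the primary outcome measures", and those measures are PTSD symptom severity and awakening cortisol profiles. On repetition it adds: "The baseline measures will be repeatedly assessed at the post test as well as the two follow-up measuring points". Hormones are therefore compared within a person across t1, t2, t3 and t4.

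The article does not fix the method by participant, visit or sample. It does not say that the method is recorded, and it does not list it as a covariate.

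**The concern.** The hormone hypotheses concern change within a person. H2 and H3 also ask whether that change goes with change in PTSD symptoms. Passive drool is unstimulated and chewing cotton is stimulated. If the two yield different measured concentrations, a participant who drools at baseline and chews at the post test shows a change that is partly method. A switch within one morning distorts the awakening rise in the same way.

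Precision on one of the two primary outcomes is at stake, together with the strength of the hormone–symptom association. The protocol can remove this source of variance before the first sample: the Trial status section reports no recruitment as of 18 June 2018.

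**Working it through.** **Plan's own figure.** The Participants section gives 159 evaluable participants at power 0.95 and a medium effect, and a target of 198 after 20% dropout. Assume f = 0.25, alpha 0.05, correlation 0.5 between time points and m = 4 time points (none of these numbers is stated). The between-group repeated-measures test with three groups then has noncentrality f²·N·m / (1 + (m−1)·0.5). At N = 158 this is 0.0625 × 158 × 4 / 2.5 = 15.8, with power 0.951; rounding to three equal groups gives 159. Dropout: 159 / 0.8 = 198.75, against the stated 198. This point disputes neither figure.

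**Added variance.** Inputs not in the documents, so assumed over a range:
- q, the share of visits at which cotton is used;
- delta, the difference between methods in SDs of the change score.

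If the method is chosen independently at each of two visits, each method indicator has variance q(1−q), and the difference between the two has variance 2q(1−q). The change variance is therefore multiplied by 1 + 2q(1−q)·delta².

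| delta | q = 0.5: multiplier | 159 is worth | q = 0.1: multiplier | 159 is worth |
|---|---|---|---|---|
| 0.3 | 1 + 0.5 × 0.09 = 1.045 | 152 | 1 + 0.18 × 0.09 = 1.016 | 156 |
| 0.5 | 1 + 0.5 × 0.25 = 1.125 | 141 | 1 + 0.18 × 0.25 = 1.045 | 152 |
| 1.0 | 1 + 0.5 × 1 = 1.50 | 106 | 1 + 0.18 × 1 = 1.18 | 135 |

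The effective number is 159 divided by the multiplier. q = 0.5 is the worst case for independent choice, because q(1−q) peaks there.

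**Other scale.** If the difference between methods, b, is expressed in SDs of a single measurement, the multiplier is 1 + 2b²q(1−q) / (2(1−rho)), where rho is the correlation between visits. At rho = 0.5 this equals the formula above. Over rho 0.3–0.7, q 0.1–0.5 and b 0.2–1.0 it runs from 1.005 to 1.83.

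**Power.** Take a three-group F test with 159 participants and power exactly 0.95 (noncentrality 15.74) and divide the noncentrality by the q = 0.5 multipliers. Power becomes 0.94, 0.92 and 0.83. As a pairwise illustration, take 53 per arm, a difference of 0.5 SD, rho 0.5 and q 0.5: power falls from 0.730 to 0.680 at b = 0.5 and to 0.556 at b = 1.0.

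**Association of changes (H2, H3).** Noise in the hormone change shrinks its correlation with symptom change by 1/√multiplier. At q = 0.5 this is 1/√1.125 = 0.943 (6% lower) for delta 0.5, and 1/√1.5 = 0.816 (18% lower) for delta 1.0.

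**Switching within a morning.** The change between visits in an awakening rise uses four samples. If the method is chosen afresh at each sample, the added term doubles to 4q(1−q)·delta², with delta now in SDs of the change in rise.

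**Bias.** In each arm let s be the share switching from drool to cotton minus the share switching from cotton to drool. The bias in the arm comparison is delta times the difference in s. A 10-point difference in s gives 0.1·delta SD. A 10-point difference in total switching with balanced directions gives none.

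**No switching.** If each participant keeps one method throughout, a constant additive offset cancels from the change score and the added term is zero.

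**The case against.** The strongest reply is that the sentence fits one method per participant as well as free choice, that handling detail often sits in a laboratory manual, and that no offset between the methods is shown. Part of this stands. A reader might infer that participants are told to use the methods interchangeably; the text does not say so. It only permits both and leaves consistency open. But this is more than silence: two methods are expressly allowed, and a manual that fixed one would disagree with the published wording. The missing offset limits the claim to a conditional one with a range, and at the low end the loss is negligible.

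Three stronger readings are not supported.

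- *The method could never be adjusted for, because the label carries only an identifier.* The article says "Tubes will be labeled with patient identifier", but this cannot be a complete list. Sample number must be known to form the profile, to restrict DHEA to three samples and to pair the hormones in the ratio. The method may likewise be recorded elsewhere, or be visible when the tube is received.
- *The protocol itself concedes that drool and cotton differ.* The sentence "Previous research has found different stimulation of salivary samples in children with chronic malnutrition" concerns differences between children by nutritional status. The protocol answers it with the waiting-list comparison, BMI and skinfold thickness. It says nothing about one collection method against the other.
- *The arm comparison is biased.* Nothing indicates that the choice of method would depend on arm. Under randomisation the expected effect is noise.

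The even split is also the least favourable case among independent choices, and stable personal habits would reduce the added variance further.

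**Conclusion.** The point holds as a conditional loss of precision. The article permits two collection methods for self-collected samples and does not hold the method constant within a participant, morning or visit. If the methods differ, switching adds variance to within-person change in cortisol and DHEA, and in their ratio unless both hormones shift by the same proportion. For independent choice at each visit the increase is 1.6% to 4.5% at delta 0.3, 4.5% to 12.5% at 0.5 and 18% to 50% at 1.0, for q from 0.1 to 0.5.

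These sizes rest on assumed values of delta and q. The documents support neither a particular size nor a bias between arms. The CAPS-CA-5, the main psychological outcome, is not touched, and the stated sample size is not in question. The change is worth making because a primary outcome is exposed and the remedy is nearly free before sampling starts.

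**What to change.** In the Hormonal analysis section, replace the either–or wording with one named collection method for all participants, samples and visits. Where a participant cannot use it, keep the alternative fixed for that participant throughout. Record the method with each sample, so that any exception can enter the model as a covariate.

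With a single method the added variance term is zero. The cost is a change of wording, one record field and a small number of exceptions to manage.

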#### Physical performance measures

In the *Shuttle Run Test* the participants have to run alternately between two lines that are 20 m separated from each other. The running speed will be given by intervals between tone signals. The interval between those signals will be reduced at every level. At the beginning of the test, the running speed is 8 km/h. Every minute it will increase by 0.5 km/h. One minute is roughly equivalent to one level of the shuttle run test. Every time the acoustic hint sounds, the participants have to reach the line. When a subject does not reach the line twice in a row, the test will be over for them. The graduated mileage will be noted and the appropriate VO_2max_ level can be read off [25].

The *International Physical Activity Questionnaire - Short Form* (IPAQ-SF; [60]) captures the general physical activity level of individuals by calculating the time of moderate and vigorous physical activity as well as the time that the participants spend walking and sitting. The questionnaire had also been used in an African context [61] and refers to the last 7 days.

The BMI will also be calculated by taking the body weight in kilograms and dividing it by the height [62].

The total body fat will be determined by using a skinfold caliper.

A detailed list of all measuring instruments and the times points at which they will be assessed is given in Fig. 2.

#### Assessment

Due to the expected low experience with mental health-related questions in the target populations, all psychological instruments will be administered as semi-structured clinical interviews held in Kiswahili. The study and clinical interviews will be conducted by a team of experienced master of science students (psychology) from both Mbarara University and Bishop Stuart University in southwestern Uganda. The research team will be extensively trained in the concepts of mental disorders, data collection, and interviewing techniques for a period of 3 weeks, both through in-person training and regular Skype meetings. Additionally, trained, bilingual, English-speaking local interpreters will be trained alongside experienced clinical and counseling psychology students in clinical interviewer skills to support the assessments. This procedure has already been successfully used in other projects of HA and RW and has proven its validity in various mental health studies in East African samples. The team of investigators will also receive constant supervision by HA and RW, both clinical psychologists/psychotherapists with extensive experience in the conduction of studies in sub-Saharan post-conflict settings.

The psychological measures have already been successfully applied in other refugee samples in resource-poor settings by HA and RW. The translation process for those measures that have not yet been translated into Kiswahili involves forward translations by two bilingual clinical psychologists, synthesis, back translation by two different experts, comparison and agreement on translation and review, and modification by a team of local experts, local assistants from the refugee community, and the principal investigators (PIs). The procedure also involves a piloting program involving juvenile DRC refugees to identify problematic phrases in the informed consent form, the instructions, and the items. This translation procedure is commonly used in studies focusing on mental health issues in similar samples and has proven its validity.

#### Initial procedure

This study will purposively select 198 refugee adolescents using the quota sampling procedure that considers the proportions of different sexes. Hence, the sample will constitute 99 female and 99 male adolescent refugees each. Every third household in each selected zone will be selected as the target household until the desired number of participants is reached. Before the interview, content, procedure, risks, the right to withdraw, and confidentiality will be explained to each participant and written informed consent (signature or fingerprints in case of illiteracy) will be obtained. In addition to their parents, children, and adolescents will also be asked to give their informed consent. Potential participants as well as their legal authorized representatives will be fully informed about the study aims, the possible inconveniences of the clinical interview procedures, the compensation for participation, and the eligibility conditions of the treatment trial. After obtaining informed consent, participants will be screened regarding (1) their PTSD symptom severity, (2) potential exclusion criteria, in particular suicidality and psychotic symptoms according to the M.I.N.I., and (3) child protection issues according to their reports in the trauma event list and their clinical appearance during their contact with the care-takers and the interviewers. Participants with noticeable problems will receive a second check up by one of the PIs and will receive referrals if action is required. The screening will take about 60 min. Participants who are eligible for inclusion in the treatment trial will attend a more in-depth assessment that will take about 80 min. Afterwards, they will be randomly assigned to one of the three interventions.

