**Methods/design:**

In a randomized controlled trial, 198 adolescent participants aged 13–16 years from the DRC who, suffer from PTSD, will be investigated. The participants are based at the Nakivale refugee settlement, an official refugee camp in Uganda, Africa, which is among the largest in the world. The participants will be randomized into an *Exercise Training (ET) group* with a maximum heart rate (HR_max_) of > 60%, an *Alternative Intervention (AI) group* with low-level exercises, and a *Waiting-list Control (WC) group*. After the 8-week interventional phase, changes in cortisol awakening response (CAR) and DHEA in the ET group that correspond to an improvement in PTSD symptoms are expected that remain at follow-up after 3 months.

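### The figure 198 is used both for adolescents selected before PTSD screening and for adolescents with PTSD entering the trial, and it contains no allowance for those found ineligible

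*Protocol article*

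**What the plan says.** The protocol article uses 198 in two ways.

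- **Before screening (Initial procedure).** "This study will purposively select 198 refugee adolescents using the quota sampling procedure that considers the proportions of different sexes". The split by sex is attached to the same group: "Hence, the sample will constitute 99 female and 99 male adolescent refugees each". Households are sampled as follows: "Every third household in each selected zone will be selected as the target household until the desired number of participants is reached". Consent comes next, and then: "After obtaining informed consent, participants will be screened regarding (1) their PTSD symptom severity, (2) potential exclusion criteria". Only a subset goes further: "Participants who are eligible for inclusion in the treatment trial will attend a more in-depth assessment that will take about 80 min". Random assignment follows that assessment.
- **After screening (Abstract and Participants).** The Abstract says that "198 adolescent participants aged 13–16 years from the DRC who, suffer from PTSD, will be investigated". The Participants section limits the trial to adolescents with a PTSD diagnosis. It gives 159 as sufficient for power 0.95 and targets 198 to allow for 20% dropout.

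Study design adds a third description. The first step is "a PTSD screening in a large and representative sample of juvenile refugees", whose purpose is to find those eligible for the intervention and to compare physical activity levels across PTSD severity. No size is given for it.

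**The concern.** If 198 adolescents are selected and only some of them are eligible, fewer than 198 can be randomised. The sample-size calculation, however, needs all 198 to be randomised, because the only loss it allows for is dropout afterwards. A field team working from Initial procedure alone could stop recruiting at a point that does not deliver the planned analysis number.

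The two sections also describe the screening sample differently. Study design calls it representative and uses it to identify variables to balance. Initial procedure describes purposive quota selection with a fixed equal split by sex, and combines this with taking every third household, which is a systematic method. As they stand, these do not describe one sampling scheme.

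**Working it through.** **Inputs from the article.** Required number 159, dropout 20%, target 198, power 0.95 and a medium effect (Participants); 198 selected before consent and screening, 99 per sex (Initial procedure); three groups (Study design). The eligible fraction, written *e* below, is not given and is varied as an assumption.

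**1. The plan's own figure.** Dropout inflation: 159 / (1 − 0.20) = 198.75. The article states 198, which agrees to within rounding. In reverse, 198 × 0.8 = 158.4, so 198 randomised leaves about 158 completers.

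The base number can also be reproduced. For a between-group effect in a repeated-measures ANOVA, the noncentrality is λ = f²·N·m / (1 + (m − 1)ρ). With f = 0.25, three groups, m = 4 time points, ρ = 0.5 and alpha 0.05, power first reaches 0.95 at N = 158, or 159 as a multiple of three (power 0.952 at 159). The article states neither alpha nor ρ, gives the effect only as medium, and does not say how many time points entered the calculation. These settings are therefore assumptions that happen to match 159. The calculation is not in question here.

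**2. What 198 contains.** The step from 159 to 198 is used up entirely by dropout. Nothing is left for refusal of consent, absence of PTSD, or the exclusions.

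**3. Initial procedure taken literally.** Randomised = 198·*e*; completers = 198·*e*·0.8. Power is from the model in step 1.

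| Assumed *e* | Randomised | Completers (159 needed) | Power |
|---|---|---|---|
| 1.0 | 198 | 158 | 0.95 |
| 0.9 | 178 | 143 | 0.93 |
| 0.8 | 158 | 127 | 0.89 |
| 0.5 | 99 | 79 | 0.70 |

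The direction is the same for every *e* below 1. The size runs from modest to severe, depending on a fraction that the document does not supply.

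**4. Initial procedure read as 198 randomised.** The number to screen is 198 / *e*: 220 at 90%, 248 at 80%, 396 at 50%. No screening number is stated, but a sample larger than 198 is what Study design describes.

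**5. Which use fits the rest of the article.** The ET section has two trainers instructing classes of 25–35. If each takes one class, the arm holds 50–70. With equal allocation (assumed), 198 / 3 = 66. This fits 198 as the number randomised, in line with the Abstract and Participants.

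**The case against.** The strongest reply is that this is loose wording and not a plan to under-recruit. Household sampling runs until a desired number is reached, and the only target defined in the article is the trial target of 198. The Abstract says that the 198 have PTSD, Study design has a separate large screen, and the class sizes fit 66 per arm. Read together, 198 is the trial sample and screening continues until it is filled.

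That reading is possible and probably intended, but Initial procedure does not state it. The only number in that section is 198 selected, and the section applies the word participants to people who have not yet been screened: "After obtaining informed consent, participants will be screened regarding (1) their PTSD symptom severity". Nothing says that sampling continues until 198 are eligible.

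Three parts of the reply stand:

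- A reader might infer that the trial will randomise far fewer than it needs. That requires a low eligible fraction, and the documents give none.
- A reader might infer that the screening sample is not large. That holds only if 198 is the screening sample; if 198 is the trial sample, the screen has no stated size and cannot be called small.
- An equal sex split does not bias a randomised comparison.

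The participant flow diagram is not visible in the text reviewed and may separate screened, eligible and randomised. The absence of those counts is therefore not held against the plan. The point is the conflict between sections that can be read.

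**Conclusion.** The inconsistency is real and concerns a figure on which the trial's power rests. Initial procedure attaches 198 and the 99/99 split to adolescents selected before consent and screening, while the Abstract and Participants attach 198 to adolescents with PTSD entering the trial. Both can hold only if every selected adolescent consents, has PTSD and meets no exclusion. Study design's description of a large screen to find eligible participants makes that implausible.

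On the literal reading, a shortfall is certain for any eligible fraction below 1, but its size cannot be determined from the documents. The completer counts assume the stated 20% dropout and an illustrative fraction; the power figures also assume the model settings listed above. The documents do not support a claim that the shortfall will be large, nor any criticism of the sample-size calculation itself. The differing descriptions of the screening sample also need reconciling.

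**What to change.** Four changes of wording:

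1. In Initial procedure, state that 198 is the number of eligible adolescents with PTSD to be randomised, and that screening through every third household continues until that number is reached.
2. State whether the 99/99 split is kept. If it is, define it as a quota on those randomised, with recruitment of a sex closing at 99, and not as a quota on the screening sample.
3. Describe the screening sample as a systematic household sample in place of a purposive quota sample, or drop the claim in Study design that it is representative.
4. It would help to add a planning number to screen, 198 divided by an assumed eligible fraction, with that assumption stated.

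The cost is small. Trial status reports no recruitment as of 18 June 2018, so on the document's own account the change came before any enrolment. The downside is that more adolescents are screened than Initial procedure implies, which Study design already foresees. If the sex quota is kept, filling the slower sex may lengthen recruitment.
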